#### Statistical analysis

Statistical analyses will be independently performed by the Biostatistics Department of University of Lille under the responsibility of [name]. Data will be analysed using SAS software (SAS Institute Inc, Cary, NC, USA) and all statistical tests will be performed with a two-tailed alpha risk of 0.05. A detailed statistical analysis plan will be written and finalised prior to the database lock. Baseline characteristics will be described for each group. The quantitative variables will be expressed as mean and standard deviation in cases of normal distribution and median and interquartile if not. The normality of distributions will be checked graphically and using the Shapiro-Wilk test. Qualitative variables will be expressed as frequencies and percentages.

For the main objective, the blood loss measured in each experimental group (low-dose and high-dose) will be compared to that of the placebo group by using an analysis of covariance adjusted for baseline blood loss volume and centre effect. In cases of non-normal distribution (except if a log-transformation could be applied to normalise the data), relative blood loss volume will be calculated and compared using a Mann-Whitney *U* test.

Analyses will be done on an intention-to-treat basis especially concerning the patients receiving a rescue dose of TA in cases of severe (>1500 mL) haemorrhage. An exploratory analysis will be performed on all the measures of the primary endpoint (T0, T30, T60, T120 and T360). We will use the linear mixed model in order to compare the evolution of the primary endpoint according to each experimental group and the placebo group. This model allows the performing of an analysis of variance (ANOVA) test for repeated measures taking into account the correlation between the repeated measures. The choice of the covariance model will be based on the AIC criteria. Post hoc analysis at each time of measure will be performed using a Bonferroni correction.

For the secondary objectives, secondary endpoints will be compared between each experimental group and the placebo group by using the chi-square test or Fisher’s exact test for qualitative parameters, and using Student’s *t* test or the Mann-Whitney *U* test for quantitative parameters. For the quantitative parameters measured at each time, we will employ the linear mixed model, as previously described for the main objective. The incidence of adverse events will be analysed in a descriptive way.

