**Methods/design:**

The current study proposal is a blinded, randomised controlled trial with the primary objective of determining superiority of either 1 g of TXA or 0.5 g of TXA, in comparison to placebo, in terms of 30% blood-loss reduction at 6 h after non-emergency haemorrhagic caesarean delivery (active PPH > 800 mL) and to correlate this clinical effect in a pharmacokinetics model with fibrinolysis inhibition measured by an innovative direct plasmin measurement regarding plasmatic TA concentration.

A sample size of 342 subjects (114 per group) was calculated, based on the expected difference of 30% reduction of blood loss between the placebo group and the low-dose group, out of which 144 patients will be included blindly in the pharmaco-biological substudy. A non-haemorrhagic reference group will include 48 patients in order to give a reference for peak plasmin level.

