### Statistical method

#### Sample size calculation

The sample size computation is based on the expected difference between the placebo group and the low-dose group and available data on the TA use in active PPH.

Ducloy et al. recruited patients who experienced moderate PPH after a vaginal delivery. The treatment was a TA uniform high dose: 4 g over 1 h, then 1 g/h over 6 h. T0–T360 blood loss after inclusion was estimated at 133 ± 252 mL (mean ± standard deviation) in the placebo group and at 58 ± 96 mL in the treated arm. Kolsi et al. recruited patients who experienced moderate PPH during CS and tested a uniform TA dose of 10 mg/kg. The TA group received 10 mg/kg of TA as an induction dose within 12 min after second-line uterotonic drug onset and 1 mg/kg/h as maintenance within the two following hours. The placebo group received the same volumes of normal saline. The average of total bleeding was 1313 ± 1432 mL in the TA group vs 2089 ± 1556 mL in the placebo group (*p* = 0.03). The WOMAN trial recruited patients who experienced bleeding after vaginal delivery or CS [24]. The design of the WOMAN trial used a 1-g single TA dose. There was no volume measurement request in the study design. The recruitment concerns mostly low-resource countries and the criterion was hysterectomy and/or mortality rate. The first results led to more than 4% and 2%, respectively, of the primary criterion, 10 times higher than European morbidity rates that cannot be extrapolated.

Given that there is no available data on the impact of low TA dosage on blood-loss reduction after inclusion, and considering a maximal 50% reduction as previously observed after higher dose administration, the required number of subjects is 103 by group for a type I error of 5% and 80% power. Considering a maximum of 10% of dropouts or missing data, we will recruit 114 haemorrhagic patients by group for a total of 342 patients.

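### Both doses are tested against one placebo arm at two-sided 0.05 with no stated order or adjustment, so as written the familywise error of the primary objective is about 9.1%, not 5%

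*Protocol article*

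**What the plan says.** The Methods/design part of the article's abstract gives the "primary objective of determining superiority of either 1 g of TXA or 0.5 g of TXA, in comparison to placebo". Under Statistical analysis, for the main objective, "the blood loss measured in each experimental group (low-dose and high-dose) will be compared to that of the placebo group" by analysis of covariance, with a rank test as fallback. The same section sets the level: "all statistical tests will be performed with a two-tailed alpha risk of 0.05".

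One multiplicity correction is named there, and it belongs to the exploratory repeated-measures model: "Post hoc analysis at each time of measure will be performed using a Bonferroni correction". Nothing is said about how the two dose comparisons combine into a conclusion.

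Under Sample size calculation, "The sample size computation is based on the expected difference between the placebo group and the low-dose group", and "the required number of subjects is 103 by group for a type I error of 5% and 80% power". A detailed statistical analysis plan is promised before database lock; it is not available here.

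**The concern.** The stated objective offers two routes to a positive finding, and both use the same placebo patients. Each route is given the full 5%, so the chance that at least one opens by luck exceeds 5%. The article corrects for multiplicity in an exploratory analysis but not in the confirmatory one, so a reader cannot assume that an unstated rule protects the primary claim.

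The exposed result is the one that matters most to a dose-finding trial: one dose significant and the other not. If that dose has a p-value between 0.025 and 0.05, the finding would be significant as the article is written but not under Hochberg. A dose recommendation would then rest on a result that is open to challenge.

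**Working it through.** **Inputs.** From Statistical analysis: two primary comparisons, a shared placebo arm, two-sided 0.05 each. From Sample size calculation: 103 evaluable patients per group, equal arms, 80% power. The same section gives the means and SDs: "T0–T360 blood loss after inclusion was estimated at 133 ± 252 mL (mean ± standard deviation) in the placebo group" and "58 ± 96 mL in the treated arm".

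**Step 1: reproduce the plan's figure.** The difference is 133 − 58 = 75 mL. The average variance is (252² + 96²)/2 = 36,360, so SD = 190.7 mL. Then

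n = 2 × (1.960 + 0.842)² × 36,360 / 75² = 101.5, which rounds up to 102 per group.

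The exact t-test calculation gives 103, the stated figure. At a per-test level of 0.025 the same inputs need 123 (normal formula) or 125 (t-test). So 103 corresponds to an unadjusted 5% for one pair of arms.

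**Step 2: correlation of the two tests.** With equal arms and common variance σ², each dose-minus-placebo difference has variance 2σ²/n. The two differences share the placebo mean, so their covariance is σ²/n and their correlation is 0.5.

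**Step 3: familywise error as written.** Take (Z₁, Z₂) bivariate normal with correlation 0.5 and neither dose effective.

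- Either direction: 1 − P(|Z₁| < 1.96 and |Z₂| < 1.96) = 1 − 0.9093 = 0.0907. Simulation of 200,000 trials gives 0.0900. Independent tests would give 1 − 0.95² = 0.0975.
- False claim of benefit for at least one dose: 1 − P(Z₁ < 1.96 and Z₂ < 1.96) = 1 − 0.9546 = 0.0454, against a nominal 0.025.

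**Step 4: candidate rules.** Familywise error under the same null is 4.6% with Bonferroni (0.025 each), 4.8% with Hochberg (simulated), and 5% with Dunnett by construction (critical value 2.212, about 0.027 per test). A fixed sequence with each test at 0.05 cannot exceed 5%, because the second test is made only if the first rejects.

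**Step 5: power for the 0.5 g claim.** Start from 80% unadjusted power, a standardised shift of 1.960 + 0.842 = 2.802 for 0.5 g, and let the 1 g effect be a multiple of the 0.5 g effect (simulated, correlation 0.5).

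| 1 g effect relative to 0.5 g | Hochberg | Fixed sequence, 1 g first |
|---|---|---|
| 1.25 times | about 79% | about 77% |
| equal | 77.5% | about 69% |
| 0.75 times | about 75% | not tabulated |
| none | 71.5% | almost none |

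For comparison, Bonferroni leaves about 71% and Dunnett about 72%, whatever the 1 g effect.

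**The case against.** The strongest reply is that a condensed article may leave the rule for combining two primary comparisons to the analysis plan. A general significance-level sentence does not exclude a hierarchy: a fixed sequence with each test at 0.05 fits the printed wording exactly, and Hochberg's first step also uses 0.05. This part stands. A reader might infer that the trial is committed to a 9% procedure, or that the analysis plan has no rule. The document supports neither reading. It shows only that no order or adjustment is stated and that, followed as printed, the error is about 9.1%. That still needs correcting, because the level is given for every test and the one correction named is placed elsewhere.

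Second, the success rule is partly inferred. The word either comes from the abstract; the body speaks of finding the optimal and minimal dose and sizes the trial on the low dose. No passage says in terms that one winning dose makes the trial positive. But the main-objective analysis does compare each dose with placebo, so the reading is reasonable.

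Third, a reader might take 9.1% as the chance of wrongly declaring the drug beneficial. It is not: it counts false findings of harm as well. The benefit-only figure is 4.5% against 2.5%, which is still nearly double.

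Fourth, a reader might infer that the quoted 5% is a false trial-wise statement, or that the trial must grow. The 5% was computed for one pair and is correct for that pair. Enlargement follows only if each test is to keep 80% power at 0.025.

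**Conclusion.** The point holds in this form: as written, the primary objective has a familywise two-sided error of about 9.1%, or 4.5% against 2.5% for a false claim of benefit. The only type I error quoted, 5%, belongs to a single comparison. These figures assume equal arms, approximately normal test statistics and no effect of either dose. If exactly one dose is ineffective, the chance of a false claim for that dose is the ordinary 5%.

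The power figures depend on the unadjusted low-dose power being 80%. The plan's inputs give that at 103 per group for a 75 mL difference. Whether that difference is a sound planning assumption is a separate question, and the familywise error does not depend on it.

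**What to change.** Before database lock, add a sentence to the protocol or analysis plan stating that the two dose-placebo comparisons of the primary endpoint form one family controlled at two-sided 5%, and name the rule. Two suitable choices are:

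- **Hochberg:** claim both doses if the larger p-value is below 0.05; otherwise claim only a dose with p below 0.025.
- **Fixed sequence:** name the order of the two doses in advance and test each at 0.05, the second only if the first is significant.

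Qualify the sentence that sets 0.05 for all tests accordingly, and restate power for the chosen rule.

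Neither choice needs more patients, but neither is free. Hochberg costs the low-dose comparison about 1 point of power if 1 g is 1.25 times as effective, 2.5 points if effects are equal, 5 points if 1 g is 0.75 times as effective, and 8.5 points if 1 g does nothing. With 1 g tested first, the 0.5 g claim drops to about 69% with equal effects and is almost unattainable if 1 g has no effect. With 0.5 g tested first, its 80% is kept and the loss moves to the 1 g claim (about 69% with equal effects, by symmetry). Because the trial is sized on the low dose, the sponsor should weigh these figures before fixing the rule, and do so without sight of unblinded data.

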### Study outcomes

#### Primary endpoint

The primary endpoint is the additional blood loss volume measured between inclusion (T0) and 6 h after inclusion (T360).

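### The primary analysis can move, on a normality check, to a test without centre adjustment on an undefined relative blood loss; one covariate-adjusted analysis of additional volume should be fixed instead

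*Protocol article*

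**What the plan says.** All references are to the protocol article.

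- **Endpoint** (Primary endpoint): "The primary endpoint is the additional blood loss volume measured between inclusion (T0) and 6 h after inclusion (T360"), a volume in mL.
- **Planned analysis** (Statistical analysis): each dose is compared with placebo by "an analysis of covariance adjusted for baseline blood loss volume and centre effect".
- **Switch** (same section): the trigger is a failed normality check that taking logs cannot repair. When it applies, the plan is that "relative blood loss volume will be calculated and compared using a Mann-Whitney" test. The order is therefore raw-scale ANCOVA, then log-scale ANCOVA, then Mann-Whitney on relative volume.
- **How the switch is decided** (same section): "The normality of distributions will be checked graphically and using the Shapiro-Wilk test". No threshold is given, nor whether raw values or residuals are checked, nor whether arms are checked separately or together.
- **Planning data** (Sample size calculation): T0 to T360 loss in the vaginal-delivery trial was "133 ± 252 mL (mean ± standard deviation) in the placebo group and at 58 ± 96 mL in the treated arm".
- **Randomisation** (Description of the unit dose, packaging and labelling of the study drug): the randomisation table is drawn up by centre.

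**The concern.** The last step changes several things at once, and the outcome data decide whether it is taken.

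1. **The variable.** Additional mL becomes a relative volume. The article does not say relative to what: T0 loss, total loss or something else.
2. **The covariates.** A Mann-Whitney test takes none. Centre, by which randomisation is organised, is lost. T0 loss survives only if relative means divided by T0 loss, and then only through a ratio.
3. **The result.** No effect estimate is attached to the test, although the abstract frames the objective as a 30% reduction and the sample size appears to rest on a difference in mean mL.

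At stake is whether the trial's main result is a statement about its declared endpoint, and whether a reader can tell beforehand which analysis will carry it. Because the normality check is partly graphical, the switch also leaves room for judgement in the primary comparison.

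**Working it through.** **Step 1. The plan's own sample size.** Inputs: 133 (SD 252) and 58 (SD 96) mL, two-sided alpha 5%, power 80%.
- Difference: 133 − 58 = 75 mL.
- Pooled SD: √((252² + 96²)/2) = 190.7 mL.
- n = 2 × (1.960 + 0.842)² × 190.7² / 75² = 101.5, so 102 per group; the usual t correction of about one gives the stated 103. Power at 103 is 0.806.

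The figure is consistent with a difference in absolute mean volume, not with a relative volume or a rank comparison.

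**Step 2. Will raw-scale normality hold?** Blood loss cannot be negative. Under a normal distribution the share below zero is Φ(−mean/SD):
- 133, SD 252: Φ(−0.528) = 29.9%.
- 58, SD 96: Φ(−0.604) = 27.3%.
- 2089, SD 1556 (total bleeding, placebo arm of the caesarean trial cited for the sample size): Φ(−1.343) = 9.0%.

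In simulated lognormal and gamma data matched to these three mean and SD pairs, Shapiro-Wilk at 0.05 rejected the raw data in 100% of samples of 103. Leaving raw-scale ANCOVA is close to certain.

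**Step 3. Will the log step hold?** The article gives neither the shape, nor the share of women with no further loss, nor the constant added before taking logs. All three are assumptions here. The lognormal matched to 133, SD 252 has log-scale SD √ln(1 + (252/133)²) = 1.234 and median 62 mL. Shapiro-Wilk rejection rates at 0.05 on log(x + 1):

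| Share of zeros | n = 103 (one arm) | n = 309 (three arms) |
|---|---|---|
| 0% | 6% | 9% |
| 2% | 41% | 89% |
| 5% | 87% | 100% |
| 10% | over 99% | 100% |

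The constant matters as much. With 3% zeros and n = 103, rejection is 65% with +1, 5% with +5 and 31% with +10. At n = 309 it is 99%, 34% and 97%. Gamma data without zeros fail the log check in 78% (2089, SD 1556) to 100% (133, SD 252) of samples of 103.

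The chance of reaching the fallback therefore runs from about 5% to about 100%.

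**Step 4. What the fallback costs.** Simulation with 103 per arm, an assumed 35% effect, and Mann-Whitney on the ratio to T0 loss against a rank-ANCOVA with T0 loss and centre:
- No covariate effect: power 0.68 against 0.69.
- Baseline correlation 0.5 and log-scale centre SD 0.5: 0.71 against 0.79.
- Type I error of each test: about 0.04 to 0.06.

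The loss is thus about 0 to 8 points, depending on covariate effects that are assumed.

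**Step 5. How far the ratio carries baseline.** If relative means divided by T0 loss, and T0 loss is assumed to be 800 mL plus a skewed excess averaging 200 mL, the rank correlation between additional loss and the ratio is 0.99. The order of patients hardly changes. So the ratio would do little harm to the ranking, but it would also do little of the work of a baseline adjustment.

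**The case against.** The strongest reply is that the sequence is written down in advance and that its middle step is sound. A log-scale ANCOVA keeps both covariates and the declared endpoint, and with lognormal data and no zeros it fails the check in only about 6% of samples of 103. The article gives no share of zeros. Women enter at 800 mL or more, and drapes and pads are weighed at each observation time, so an exact zero over six hours cannot be presumed. A detailed analysis plan is promised before database lock, where the log constant, the check's threshold and the meaning of relative would normally appear. The harm shown is also modest.

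Much of this stands. A reader might infer that the Mann-Whitney test is likely to become the actual analysis; the documents do not support that, since Step 3 gives almost any probability. A reader might also infer that baseline loss is ignored; that depends on what relative means. Nor is it right that no result in mL will exist: the article reports non-normal variables by median and interquartile range and plans an exploratory mixed model that includes T360. What is missing is an estimate tied to the fallback comparison.

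The deferral argument does not remove the point. The article states the switching rule itself, and defining its terms later would still leave the endpoint and the adjustment dependent on a normality check.

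**Conclusion.** The point holds in this limited form: the stated rule lets a normality check replace an adjusted analysis of the declared endpoint with a test on an undefined variable that drops the centre adjustment. That raw-scale ANCOVA will be abandoned follows almost directly from the article's own SDs, provided they resemble those of this trial. How often the last step is reached is unknown, from about 5% to about 100% under the assumed shapes, zero shares and constants.

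This is not a finding of inflated false positives: each test holds its level at about 0.04 to 0.06. In the simulations the fallback and the adjusted rank analysis disagreed on significance in 5 to 14% of trials; a reader might take that as an error rate, but it is ordinary disagreement between two valid tests. The power loss is modest (about 0 to 8 points) and uncertain, because on skewed data a rank test can be more efficient than a raw-scale one. The main cost is that the primary variable and method are not fixed. Severity: should-fix, as a cheap improvement.

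**What to change.** Before unblinding, in the protocol and the analysis plan:

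1. Remove the normality-driven switch for the primary comparison.
2. Name one primary analysis of additional blood loss volume, T0 to T360, that tolerates skew and zeros and keeps T0 blood loss and centre. Suitable choices are rank-ANCOVA, a proportional-odds model, or ANCOVA on log(volume + a constant fixed in advance) with robust standard errors, kept whatever the normality check shows. The choice among them is open.
3. Report an adjusted effect estimate with its confidence interval.
4. Define relative blood loss and move it, with the Mann-Whitney test, to a sensitivity analysis.

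The cost is wording only: no new data, covariates already planned, and no change forced on the 103 per group. The downside is model output that is slightly less familiar to clinical readers.

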#### Randomisation, blinding and treatment administration – blind production of TA doses and their concentration and stability assessment

##### Description of the unit dose, packaging and labelling of the study drug

The doses will be packaged blindly for the investigators by the pharmacy of the sponsor. Each package will be numbered following the randomisation table established by centre. The package will include 10-mL syringes or flacons of the studied product. The preparation of the product in each group will be TA1 (10 mL = 1 g TA + 0 mL saline), TA½ (5 mL = 0.5 g TA + 5 mL saline) or TA0 (0 mL = 0 g TA + 10 mL saline). The master randomisation list is furnished to the pharmacy production unit to identify the packages by identification numbers containing information on the centre, on the haemorrhagic or non-haemorrhagic groups, and the inclusion number of the patient. Numbers appears clearly on packages and labels for researchers and laboratory. Unblinding envelopes are available in cases of emergency.

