#### Secondary clinical endpoints

The secondary endpoints will measure the impact of the study product and dose on total blood loss, intensity and rate of postoperative anaemia (decrease of haemoglobin preoperative to day 2, nadir of haemoglobin, number of patients with haemoglobin under 8 g/dL or a 4-point decrease at any time), immediate and late red blood cell transfusion and usage of prohaemostatic products, rate of surgical interventional procedures, such as arterial ligature, or surgical compression of the uterine wall or internal compression balloon, CS duration and general anaesthesia frequency, rate of postoperative organ failure, rate and duration of intensive care hospitalisation, breast-feeding duration, death, and the safety of the dose-ranging use of TA in haemorrhagic CS, and side effects related to the product.

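### Secondary endpoints get unadjusted tests although T0 blood loss and centre are in the primary model, and the exploratory blood-loss model uses T0, where additional loss is zero, as a response

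*Protocol article*

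**What the plan says.** All references are to the protocol article.

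- **Primary analysis** (Statistical analysis): each dose is compared with placebo "by using an analysis of covariance adjusted for baseline blood loss volume and centre effect".
- **Secondary analyses** (same section): "secondary endpoints will be compared between each experimental group and the placebo group by using the chi-square test" or Fisher's exact test for qualitative variables, and "using Student’s *t* test or the Mann-Whitney *U* test for quantitative parameters". No covariate is named. Quantitative parameters measured at every time go into the linear mixed model, again with no covariate named.
- **Allocation** (Description of the unit dose, packaging and labelling): "Each package will be numbered following the randomisation table established by centre".
- **Secondary endpoints** (Secondary clinical endpoints): "The secondary endpoints will measure the impact of the study product and dose on total blood loss", followed by the haemoglobin decrease to day 2, nadir haemoglobin, transfusion and others. Under Study population, women enter the experimental groups only once they have lost at least 800 mL.
- **Repeated measures**: under Primary endpoint, "The primary endpoint is the additional blood loss volume measured between inclusion (T0) and 6 h after inclusion (T360"). Under Statistical analysis, "An exploratory analysis will be performed on all the measures of the primary endpoint (T0, T30, T60, T120 and T360"), with the covariance model chosen by AIC; then "Post hoc analysis at each time of measure will be performed using a Bonferroni correction".

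**The concern.** There are two separate problems.

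**Secondary tests.** Blood lost before injection cannot be altered by treatment. It is nevertheless part of total loss, and plausibly feeds the haemoglobin drop (referenced to a value before delivery), nadir haemoglobin and transfusion. T0 loss is measured and the primary model already uses it, so leaving it out of the secondary tests leaves removable variation in the error term. Leaving out centre also ignores the factor by which allocation was organised. A positive primary result could then sit beside an inconclusive result on total loss for no reason other than variation between women before treatment.

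**T0 as a response.** Additional loss since T0 is 0 mL at T0 for every woman. A response with no variance makes an unstructured covariance singular and makes any equal-variance structure wrong. A post hoc test at T0 has no content but still uses a share of the Bonferroni correction.

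**Working it through.** **1. The plan's own figure.** Inputs (Sample size calculation): additional loss to 6 h of 133 ± 252 mL on placebo and 58 ± 96 mL on treatment in the cited vaginal-delivery trial.

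- Root-mean-square SD = √((252² + 96²)/2) = 190.7 mL; difference = 133 − 58 = 75 mL.
- n = 2 × (1.960 + 0.842)² × 190.7² / 75² = 101.5, so 102 per group; the t-based version gives 103, the stated number.

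**2. Variance ratio for total loss.** Write total = T0 loss (SD s_B) + additional loss (SD s_A), with correlation r between them.

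- Unadjusted variance: s_A² + s_B² + 2·r·s_A·s_B
- Variance adjusted for T0 loss: s_A²(1 − r²)

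*Assumptions:* s_B of 150 to 350 mL and r of 0 to 0.3. The protocol gives neither. It does offer two very different scales for the blood-loss SD.

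(a) s_A = 252 mL (placebo arm, vaginal delivery):
- s_B 150, r 0: (63,504 + 22,500)/63,504 = 1.35; 103 per group act like 76.
- s_B 350, r 0.3: (63,504 + 122,500 + 52,920)/(63,504 × 0.91) = 238,924/57,789 = 4.13; 103 act like 25.
- If T0 loss clusters near the entry threshold (s_B 50 or 100, r 0): 1.04 or 1.16.

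(b) Total SD = 1556 mL (placebo arm of the cited caesarean trial), solving the first formula for s_A:
- s_B 150, r 0: 1556²/(1556² − 150²) = 2,421,136/2,398,636 = 1.01; 103 act like 102.
- s_B 350, r 0.3: s_A = 1414.8; 2,421,136/1,821,399 = 1.33; 103 act like about 77.

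**3. The same point as power.** With an effect of 75 mL, 103 per group and additional-loss SD 190.7 mL, and assuming a T0 SD of 100 to 400 mL and r of 0 to 0.5, the unadjusted test of total loss has 70% power (SD 100, r 0) down to 18% (SD 400, r 0.5). Adjusted for T0 loss, power is 81% (r 0) to 90% (r 0.5), whatever the T0 SD.

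**4. Validity.** In one simulated setting (centre-stratified allocation, an assumed centre effect of 100 mL per step, 4000 runs) the unadjusted t test of total loss rejected 2.1% of the time at nominal 5%. It was conservative, not inflated.

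**5. What adjusted total loss estimates.** Since total = T0 loss + additional loss, a linear model containing T0 loss gives both outcomes the same treatment coefficient over the same window. In a simulated data set, with T0 loss and centre in the model, both gave −31.73 (SE 20.96).

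**6. The T0 row.** With additional loss set to 0 at T0, the 5 × 5 covariance matrix of the five times has rank 4. To see the effect of an equal-variance structure, assume independent increments with SDs 80, 80, 100 and 116 mL, so the cumulative variances are 6,400, 12,800, 22,800 and 36,256. An equal-variance model uses their average:
- T30 to T360 only: mean 19,564. The test at T360 understates its variance by a factor of 1.85, and the error rate at nominal 5% is about 15% (simulated 14.8%).
- Adding a zero at T0: mean 15,651, factor 2.32, error rate about 20% (simulated 19.5%).

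Bonferroni over five times gives 0.05/5 = 0.0100; over four times, 0.05/4 = 0.0125.

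**The case against.** **Unadjusted tests are legitimate after randomisation.** This stands. A reader might infer bias or excess false positives in the secondary results; the documents do not support that, and the simulation shows the opposite. What remains is lost precision.

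**The protocol defers to a detailed analysis plan.** That plan could add covariates. But the protocol does more than stay silent: it names specific tests that differ from its own primary strategy, so the later plan has to change them.

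**For total loss to T360, adjustment only reproduces the primary analysis.** True, by step 5. The gain there is consistency with the primary result and not new evidence. For haemoglobin and transfusion outcomes the adjusted analysis is not a restatement, but the documents allow no estimate of the gain.

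**The size depends on chosen inputs.** Also true. A reader might take 103 per arm acting like 25 as the expected loss; it is the extreme corner of an assumed grid, built on a vaginal-delivery placebo SD. On the caesarean total-bleeding SD the ratio is only 1.01 to 1.33.

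**Blood loss may fall under the mixed-model sentence, and that model may follow cumulative loss.** If so, T0 is not zero and using it as a response is legitimate. The literal text refers to measures of the primary endpoint, which is additional loss, so the reading needs to be settled in words. Nor is the T0 row the main source of error in step 6: the rate is already 14.8% without it, and AIC selection does not commit the trial to an equal-variance structure.

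**Conclusion.** The point holds as a matter of efficiency and specification, not validity. The secondary tests discard T0 blood loss and centre, both already needed for the primary analysis. For total loss the cost is a variance ratio somewhere between about 1.01 (total SD 1556 mL, T0 SD 150 mL, correlation 0) and about 4 (additional-loss SD 252 mL, T0 SD 350 mL, correlation 0.3). The T0 SD and the correlation are assumptions, and the documents cannot narrow the range.

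Read literally, the exploratory model includes a response that is zero for everyone. That defect is confined to additional blood loss; for other repeated parameters, such as D-dimers, a T0 response is legitimate. It might be inferred that the trial's main conclusion is at risk. It is not: the primary ANCOVA is adjusted, and the repeated-measures model of blood loss is labelled exploratory.

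**What to change.** In the analysis plan, before database lock:

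1. **Continuous blood-loss and haemoglobin secondary endpoints:** ANCOVA with T0 blood loss and centre, or a rank-based or ordinal equivalent where the distribution requires it. State that total loss to T360 then gives the same treatment effect as the primary analysis.
2. **Binary secondary endpoints that are not rare:** logistic or Mantel-Haenszel analysis adjusted for centre and T0 loss, pooling small centres if data are sparse. Trial status reports 64 inclusions at the first centre and 13 across the other four, so this may be needed. Keep Fisher's test for rare events.
3. **Exploratory mixed model of additional loss:** responses at T30, T60, T120 and T360; T0 loss and centre as covariates; a covariance structure that lets the variance differ by time; Bonferroni over four times. If cumulative loss including the part before T0 is intended, say so and keep T0.
4. **Other repeated parameters:** T0 may stay as a response.

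The cost is wording and a little more modelling. T0 loss and centre are already required for the primary analysis, so no new data are needed and the sample size does not change.
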